As strength and dynamic motor-control capacities, in particular, are preventive for a re-injury [4, 5], they have to be targeted in recurrence prevention programs. Inadequate knee mechanics also result from trunk displacement and unequal limb loading [11]; thus, it is not sufficient to only target the knee joint. As an important surrogate of functional restoration of the knee and, likewise, not only triggered by the knee joint solely, avoiding a dynamic knee valgus may be crucial to prevent subsequent injury [11, 12]. Although contextual overlap between therapeutic and preventive programs (such as the described dynamic motor-control enhancement and avoidance of a dynamic knee valgus) exists, the therapeutic focus after ACL reconstruction should shift from therapy to recurrence prevention after a certain rehabilitation time. Several prevention programs exist and have been validated in terms of preventive effects on a primary ACL rupture incidence [13]. Although theoretical evidence exists that such programs may be effective in the prevention of a subsequent ACL injury [6], their effectiveness for primary and, in particular, for secondary prophylaxis after successful ACL reconstruction, is still a matter of debate. Likewise, the implementation capacity of such programs into everyday training after the prescribed rehabilitation is unknown.

The aim of the study is to assess the effects and implementation capacity of a preventive approach (Stop-X program [14]) after ACL reconstruction. Effects on re-injury-related motor-control/function, re-injury rates and time to successful RTS form the focus of this study.

The null hypothesis is as follows: the Stop-X program, as part of the evidence-based care and rehabilitation after ACL rupture and reconstruction, is not systematically superior to standard rehabilitation in terms of its effects on neuromuscular function, re-injury rate risk and time until RTS success.

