### Statistical analysis

Following range plausibility control based on potentially reachable physiological values, a visual control for non-plausible outliers will be performed. Afterwards, all analyses will be performed based on the underlying assumptions for parametric, or rather, non-parametric testing. In detail, for all difference testing, data and variance distribution (i.e., normality) are checked; for all correlation analyses, residuals, auto correlation, and heteroscedasticity, are checked. The alpha-error threshold is set at 5%, all *p* values below are considered significant.

The analyses for the primary outcome, DJST, are done confirmatory, alpha-error corrections (Bonferroni-Holm for paired and Sidak-Holm for unpaired analyses) are performed for multiple used samples and post-hoc analyses following significant omnibus testing, whilst the alpha-error remains unadjusted for the exploratory (secondary) analyses.

The main statistics are performed twice (two different data structures): once on a time-based and once on a functional-based data structure. All repeated measures statistics are thus first performed for the time-based data structure where statistics are performed on all outcomes assessed at the same real-time after reconstruction. Secondly, functional-based data-structure analyses are performed, where the first (baseline) measurement is the first “real” measurement at the time of being cleared for the assessment (varying times of 4–8 months post reconstruction). For each of the analyses on the two datasets, gain-score analyses are performed for differences from pre (baseline) to post (each following time point) of all outcomes using repeated-measures analyses of co-variance (rmANCOVAs) with potential confounders as co-variates (baseline values, injury history, sex, type and amount of sport, age, co-morbidities). In case of a systematic impact of confounders on statistics, z-transformed values are calculated and used for further analyses. Afterwards, survival analyses by means of Kaplan-Meier plotting plus between group-difference analyses using log-rank tests are performed. Hazard ratio estimations will be calculated. Events will be: (1) Time point of unrestricted RTS decision, (2) Time point of functional criterion RTS succeeded (> 60% normalized knee-separation distance at DJST) and (3) Time point of revision surgery, re-injury or subsequent injury.

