## Discussion

The primary aim of the study is to test the feasibility and effectiveness of an ACL secondary preventive intervention. To do so, a standardized diagnostic assessment and a randomized controlled, single-blind intervention design are used. The intervention consists of exercises to target deficits in motor control and dynamic knee axis steadiness. A strength of this intervention is its practicability. Furthermore, all exercises can be performed without (or only with a little) additional material.

Recurrence prevention and the according diagnostics during and after RTS following ACL reconstruction are, except in professional athletes, only adopted to a minor degree [30]. Even in professional sports, the athletes’ performance quality is decreased after return to competition [1] and the re-injury risk remains high for years after the ACL rupture [1, 2]. Consequently, and applicable in entire populations, developing and employing strategies for secondary prevention and appropriately adapted functional diagnostics are crucial. Beyond the focus on recurrence prevention, the potential of the program in pre-operative training may be given. Pre-operative training strategies are highlighted to be of importance [31], yet, they are only carried out sparsely; therefore, a feasible intervention may be helpful.

The heterogeneity of the participants may become a limitation for the results’ interpretation and the deduction of the practical relevance of our trial. To minimize this potential bias, co-variate analyses are performed. Together with the randomized study design and the resulting respect of unknown confounders, considering the known and suggested confounders provides a sufficient statistical power. A common limitation in clinical exercise trials is the limited possibility of blinding the patients. This limitation is reduced by the superiority design (no inactive control group) of our study. To further reduce the risk of bias as much as possible, all investigators are blinded to intervention allocation.

Beyond this, the results of our study will be of importance not only for researchers and policy makers, but also for patients.

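### The arm comparison for time to return to sport and time to the functional criterion is an unadjusted log-rank test: valid, but it leaves already collected prognostic covariates unused and so gives away power

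*Protocol article*

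**What the plan says.** The Statistical analysis section of the protocol article names one between-arm method for three events: (1) unrestricted RTS decision, (2) first reaching more than 60% normalized knee separation on the DJST, and (3) revision, re-injury or subsequent injury. It states that "survival analyses by means of Kaplan-Meier plotting plus between group-difference analyses using log-rank tests are performed. Hazard ratio estimations will be calculated", with no model or covariates.

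For the repeated-measures analyses the same section does specify adjustment, namely "with potential confounders as co-variates (baseline values, injury history, sex, type and amount of sport, age, co-morbidities". It makes the DJST analysis confirmatory and the secondary analyses exploratory, with unadjusted alpha.

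Two other places bear on the point. The null hypothesis in the Background is framed "in terms of its effects on neuromuscular function, re-injury rate risk and time until RTS success". The Discussion, on participant heterogeneity, says "To minimize this potential bias, co-variate analyses are performed" and adds that considering known confounders gives sufficient power.

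**The concern.** The plan treats baseline values, sex, age, injury history, sport and co-morbidities as worth adjusting for when the outcome is a score, then drops them when the outcome is a time. For event (2) the omission is most visible: the event is a threshold on DJST, so an earlier DJST value predicts it almost by construction, as long as values correlate between visits. For event (1) the covariates are plausible predictors, and the protocol itself presumes that they matter.

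In a proportional-hazards setting, leaving out a prognostic covariate lowers the power of the arm comparison even when the arms are balanced. At stake is a greater chance of missing a real difference in time to RTS or to the functional criterion. The validity of the trial and its confirmatory DJST analysis are not at stake.

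**Working it through.** **1. The plan's own figure.** The sample size section uses d = 0.3, two-sided alpha 5% and beta 50%. The normal approximation gives n per arm = 2(1.96 + 0)²/0.3² = 85.4, so 86. The exact t-test has 49.9% power at 86 and 50.3% at 87 per arm, so 87 (174 in total) reproduces. 174/0.7 = 248.6, so 249, rounded to 250. This belongs to the DJST gain-score comparison. No event count, hazard ratio (HR) or power is given for any time-to-event outcome, so every input below other than 174, SD 14.2, mean 66.4 and 0.3 × 14.2 = 4.26 points is an assumption.

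**2. Log-rank benchmark.** Assume 80% of 174 have the event (139 events). Schoenfeld power is Φ(|ln HR|·√D/2 − 1.96). At HR 1.4: 0.3365 × 11.79/2 − 1.96 = 0.02, so 51%. At HR 1.3 it is 34%, at HR 1.5 67%.

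**3. Cost of omitting one covariate.** Simulation with 174 participants, 139 events, one standard-normal covariate and 2,000 runs per row (Monte Carlo standard error about 1 point). Power is log-rank / adjusted Cox:

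| Covariate log-HR per SD | Conditional HR 1.4 | Conditional HR 1.5 |
|---|---|---|
| 0 | 52% / 52% | 67% / 67% |
| 0.3 | 48% / 50% | 63% / 68% |
| 0.5 | 41% / 51% | 56% / 65% |
| 0.8 | 33% / 49% | 43% / 66% |
| 1.0 | 29% / 51% | 37% / 67% |

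With no arm effect, rejection rates were 5.1% to 5.8% (log-rank) and 4.6% to 5.8% (adjusted). At a conditional HR of 1.4, the average unadjusted HR moved from 1.40 (no prognostic value) to 1.27 (log-HR 1.0).

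**4. Event (1), parameterised by explained variance.** Extreme-value log-times, arm effect 0.3 SD, 15% censored, 87 per arm, 1,500 runs. If the covariates explain 5%, 10% or 25% of log-time, power goes from 62% to 67%, 60% to 70%, and 53% to 77%. An unadjusted Cox test stood in for the log-rank test here and in step 5.

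**5. Event (2), adjusting for the first DJST value.** 87 per arm, SD 14.2, eight monthly visits after the first, event = first visit above 60%, participants above 60% at the first visit not at risk. Power is unadjusted / adjusted.

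(a) Drift 0.5 points per month, full 4.26-point effect at every later visit, 1,000 runs:

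| First-visit mean | Correlation 0.3 | 0.5 | 0.7 |
|---|---|---|---|
| 52.2 | 47.0 / 51.2 | 45.2 / 53.5 | 45.0 / 63.9 |
| 59 | 31.6 / 33.8 | 32.6 / 37.4 | 36.3 / 51.8 |
| 66.4 | 17.0 / 17.5 | 18.2 / 19.7 | 26.0 / 31.7 |

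With no arm effect (mean 52.2, correlation 0.5), rejection was 4.1% / 5.1%.

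(b) Control-arm mean rising linearly to 66.4 and arm difference growing linearly to 4.26 by the last visit, 400 runs: mean 50, 14% / 20% at correlation 0.5 and 21% / 42% at 0.8; mean 55, 10% / 12% and 18% / 27%; mean 60, 8% / 9% and 12% / 19%.

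Absolute levels differ because the trajectories differ; the direction does not.

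**6. When the first DJST value is taken.** In the functional-based structure "the first (baseline) measurement is the first “real” measurement at the time of being cleared for the assessment", which is 4 to 8 months after reconstruction. Randomization follows inclusion, so it may come before this value. Pre-operative measurement happens only where applicable, and already operated patients may enrol. The Study flow section also allows Stop-X to form part of pre-operative treatment. The first DJST value may therefore follow randomization and even exposure. The share above 60% at that visit, 1 − Φ((60 − mean)/14.2), would be 29%, 47% and 67% at means of 52.2, 59 and 66.4, so removing these participants from the risk set is a large restriction.

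**The case against.** The strongest reply is that the log-rank test is standard, valid in a 1:1 randomized trial and holds its error rate, so an adjusted model is an option and not a correction. That stands: a reader might infer that the planned test is wrong or biased, and neither the documents nor the simulations support it.

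The hazard-ratio sentence leaves the model open, so an adjusted Cox estimate is not excluded. This also stands, but the named test is still the log-rank test, and an adjusted estimate beside an unadjusted p-value would leave two answers. The plan also says that z-transformed values go into further analyses if confounders have a systematic impact. It does not tie this to the survival times, and standardising a variable does not adjust an arm comparison.

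Four stronger readings should be resisted:
- That the survival outcomes are planned at 50% power. That figure belongs to the DJST comparison.
- That the unadjusted hazard ratio is biased toward 1. Marginal and conditional hazard ratios are different quantities (non-collapsibility); each answers its own question.
- That the Discussion contradicts the analysis section. Its general remark on covariates is met by the repeated-measures models; it is simply not carried into the survival test.
- That adjusting for the first DJST value is always safe. Step 6 shows that it may condition on something measured after randomization.

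The sizes are also fairly challenged. The only DJST mean in the document is 66.4%, a post-intervention value from a cited trial; used as the first-visit mean, it gives gains of about 0.5 to 6 points. The event (2) runs adjust for one covariate only, so the full list was not tested there.

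**Conclusion.** The point holds as a low-cost improvement. The plan names an unadjusted log-rank test for time to unrestricted RTS and time to the functional criterion, while covariates that it regards as influential are collected and used elsewhere. The test is valid and the outcomes are exploratory, but time to RTS is in the null hypothesis and some power is given away.

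The amount cannot be derived from the documents. Under the assumptions shown it is nil if the covariates are not prognostic, a few to about 10 points at moderate strength, and roughly 20 points or more if they are strongly prognostic. For event (2) it also shrinks as the between-visit correlation falls or as the first-visit mean approaches or passes 60%. The point does not extend to re-injury, where few events are likely and leave little room for covariates.

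**What to change.** Amend the Statistical analysis section before unblinding:

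- **Event (1):** make a Cox model the main arm comparison, adjusted for a short list of covariates fixed before randomization (age, sex, injury history, pre-injury type and amount of sport, co-morbidities). Keep Kaplan-Meier curves and the log-rank test as the unadjusted description.
- **Event (2):** use the same model. Add the first DJST value as a continuous covariate, with the time origin at that visit and participants already above 60% not at risk, only where that measurement precedes the start of the arm-specific programme. Report beside it the analysis of all randomized participants without this conditioning.
- **Event (3):** keep the log-rank test, or adjust for at most one or two covariates.

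The cost is a few sentences and a few models in software already named (SPSS), with no new patients or data. There are two downsides. The adjusted hazard ratio is conditional on the covariates and so differs in meaning from the marginal one, and participants with missing covariates need a handling rule.

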## Discussion

The primary aim of the study is to test the feasibility and effectiveness of an ACL secondary preventive intervention. To do so, a standardized diagnostic assessment and a randomized controlled, single-blind intervention design are used. The intervention consists of exercises to target deficits in motor control and dynamic knee axis steadiness. A strength of this intervention is its practicability. Furthermore, all exercises can be performed without (or only with a little) additional material.

Recurrence prevention and the according diagnostics during and after RTS following ACL reconstruction are, except in professional athletes, only adopted to a minor degree [30]. Even in professional sports, the athletes’ performance quality is decreased after return to competition [1] and the re-injury risk remains high for years after the ACL rupture [1, 2]. Consequently, and applicable in entire populations, developing and employing strategies for secondary prevention and appropriately adapted functional diagnostics are crucial. Beyond the focus on recurrence prevention, the potential of the program in pre-operative training may be given. Pre-operative training strategies are highlighted to be of importance [31], yet, they are only carried out sparsely; therefore, a feasible intervention may be helpful.

The heterogeneity of the participants may become a limitation for the results’ interpretation and the deduction of the practical relevance of our trial. To minimize this potential bias, co-variate analyses are performed. Together with the randomized study design and the resulting respect of unknown confounders, considering the known and suggested confounders provides a sufficient statistical power. A common limitation in clinical exercise trials is the limited possibility of blinding the patients. This limitation is reduced by the superiority design (no inactive control group) of our study. To further reduce the risk of bias as much as possible, all investigators are blinded to intervention allocation.

Beyond this, the results of our study will be of importance not only for researchers and policy makers, but also for patients.

## Trial status

Participant recruiting started on 25 October 2018. At the time of manuscript submission, we included six participants into the study. No participant has yet completed the intervention. Screening completion is anticipated to be 15 October 2019, measurement completion by 15 October 2020 and overall study completion is expected to be May 2021.

## Data Availability

Not applicable.

## Abbreviations

ACL: Anterior cruciate ligament
ADL: Activities of daily living
DJST: Drop Jump Screening Test
DRKS: German Clinical Trials Register
IKDC-2000: International Knee Documentation Committee knee evaluation form
KOOS: Knee injury and Osteoarthritis Outcome Score
RTS: Return to sport
SD: Standard deviation
SLHD: Single-leg hop for distance
TSK: Tampa Scale of Kinesiophobia
